**TEST DRUG AND PLACEBO PREPARATION**

Vial fills of 1.0ml (10mg/ml) CPG 7909 will be shipped from Coley Pharmaceutical Group. The Hospital Pharmacy at Århus University Hospital will import, prepare and label CPG 7909 and placebo as described below. The primary investigator will advise the Hospital Pharmacy of the required amount of doses needed by faxing a complete list of study participants (by study IDs) one day before the participants are scheduled to come. The Hospital Pharmacy is responsible for the safe and appropriate storage of CPG 7909 and placebo until the doses are dispatched to the sponsor/investigator. Upon receipt of the syringes at The Department of Infectious Diseases the sponsor/investigator takes full responsibility for the safe and appropriate storage of the preparations. The Hospital Pharmacy guarantees drug sterility for 24 hours after dispatch.

TREATMENT AND STORAGE OF VACCINES, TEST DRUG AND PLACEBO

Vaccines will be kept in a refrigerator at 5° Celsius in a clearly marked rack at the Department of Infectious Diseases. Test drugs and placebo will be kept on a separate rack in the same refrigerator in identical 1 ml syringes.

**OTHER TREATMENT:** No additional medication or treatment is planned and no changes in regular medication will be made due to the participant’s inclusion in this study. Any changes in medication during the time of the study will not disqualify the individual for further participation in the study and study participation will not interfere with the HIV physician’s decision regarding HAART and other medical treatment received or initiated during the time of the study.

**ROUTE OF ADMINISTRATION:** Intramuscular injection

**BLINDING:** Double-blinded study.

##### ENROLMENT: Randomization;

Eligible patients will be randomized in a ratio of 1:1 to receive **pneumococcal vaccination with or without CPG 7909**. Random allocation lists will be generated by computer by the hospital pharmacy. A complete randomization list will be stored at the hospital pharmacy. Cluster randomization will be used to obtain similar distributions of on-HAART and HAART-naïve subjects in the two treatment arms. Subjects will be randomized in blocks of 6. Sealed envelopes revealing the subjects’ treatment allocation will be made by the Hospital Pharmacy and transferred to a safe at the Department of Infectious Diseases before initiating the study. If indicated (i.e. in the case of a SUSAR (see below)) a subject’s group allocation can be revealed without unmasking the entire study.

Participants will receive their study ID after passing inclusion/exclusion criteria (according to treatment; +HAART/-HAART). Participants will be entered into the study and given study ID according to the chronological order in which they are included (i.e. the first subject in the study will be assigned study ID #1 if HAART naïve, or study ID #43 if on HAART, the 2nd subject will receive the next available study ID according to HAART status and so fort). Registration is done by the investigator by highlighting the next available number on the entry list and by adding randomization labels to the front of the subjects CRF. Participants will be blinded to their assigned vaccine adjuvant (placebo or CPG 7909). Investigators conducting the immunization will also be blinded to the subject’s treatment allocation and to the contents of the test drug/placebo preparation.

**IMMUNIZATION**

Vaccines will be kept in their original container according to manufacturer’s description and mixed with the adjuvant immediately before immunization. The formulation of vaccine plus adjuvant/placebo will be prepared by the physician. Dosing of adjuvant/placebo and sealing of syringes will be done by the Hospital Pharmacy. Adjuvant (CPG 7909 or Placebo) will be delivered from the Hospital Pharmacy in a sealed 1 ml syringe. Each syringe will be labeled with the following information: study ID, Batch number and time+date of dispatch. Batch number and study ID will be recorded in the subject’s CRF. Immunization will be done in the left or right upper deltoid muscle at the preference of the subject.

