##### VACCINES AND TEST DRUG/PLACEBO INJECTIONS:

All subjects are dosed at 0, 90 and 270 days. All immunizations are done in the deltoid muscle of the right or left arm (according to the participants preference).

- At day 0 and 90 study participants receive one intramuscular injection of double the recommended paediatric dose of Prevenar 1.0 ml + 0.1 ml test drug (CPG 7909)/placebo. In both cases, the volume injected into the arm is 1.1 ml.
- At day 270 study participants receives one intramuscular injection of 0.5 ml Pneumo Novum + 0.1 ml test drug(CPG 7909)/placebo. In all cases, the volume injected into the arm is 1.1 ml.

Investigators and participants are not aware of whether experimental or control injection is administered. The volume and appearance of each injection product are identical. The exact product number of each test drug/placebo and batch number prepared by the hospital pharmacy will be recorded in the individuals CRF as well as the volume of any remaining fluid in the syringe .

Immunization and follow-up is conducted by investigators and study nurses at the Department of Infectious Diseases at Skejby Hospital, Aarhus University Hospital.

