**ASSESSMENT OF CAUSALITY**

The investigator is obligated to assess the relationship between the investigational product and the occurrence of each AE/SAE. The investigator will use clinical judgement to determine the relationship- Alternative causes, such as natural history of the underlying diseases, concomitant therapy, other risk factors and the temporal relationship of the event to the investigational product will be considered and investigated. The investigator will also consult the Investigator Brochure and vaccine product information in the determination of his/hers assessment.

All solicited local (injection site) reactions will be considered causally related to vaccination. Causality of all other AEs should be assessed by the investigator.

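### Batch and product numbers of test drug and placebo are visible to blinded investigators, and nothing says they are masked or common to both arms

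*Protocol*

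**What the plan says.** The trial is described as double-blinded. In the ENROLMENT section of the Protocol: "Investigators conducting the immunization will also be blinded", and the sentence goes on to cover both the allocation and what the syringe contains. The same section says that one participant's allocation can be opened while the rest of the trial stays masked.

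The Hospital Pharmacy "will import, prepare and label CPG 7909 and placebo as described below" (TEST DRUG AND PLACEBO PREPARATION), and on the list: "A complete randomization list will be stored at the hospital pharmacy" (ENROLMENT).

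On labels, the IMMUNIZATION section says: "Each syringe will be labeled with the following information: study ID, Batch number and time+date of dispatch". It continues: "Batch number and study ID will be recorded in the subject’s CRF". The section VACCINES AND TEST DRUG/PLACEBO INJECTIONS goes further: "The exact product number of each test drug/placebo and batch number prepared by the hospital pharmacy will be recorded in the individuals CRF". The vaccine and the syringe contents are mixed at the site by the physician.

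On safety outcomes, ASSESSMENT OF CAUSALITY treats every solicited local reaction as related to vaccination and then states: "Causality of all other AEs should be assessed by the investigator".

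**The concern.** The Protocol takes care that the two preparations look alike: same syringe, same volume, same colour and viscosity. It does not extend that care to the numbers attached to them. A batch or product number ordinarily identifies a preparation, and here there are two. If the number on a CPG 7909 syringe differs systematically from that on a placebo syringe, site staff hold a group label for each participant, although not at first the name of the group.

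Two things could then supply the name. One is a code break for any member of the group. The other is tolerability pooled over the group: the Background section describes dose-related local and flu-like reactions with TLR9 agonists, and a pattern too weak to classify one participant may be readable across many who share a number.

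Safety and tolerance of CPG 7909 is a stated secondary objective in a trial labelled Phase I, and several of its outcomes rest on investigator judgement. Those are the outcomes that blinding is there to protect.

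**Working it through.** The question is mainly one of reading sections together. Only the possible extent needs arithmetic.

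**1. What site staff can see.** The label carries study ID, batch number and dispatch time (IMMUNIZATION). The CRF carries the batch number and the exact product number of the test drug or placebo (IMMUNIZATION; VACCINES AND TEST DRUG/PLACEBO INJECTIONS). The physician who mixes the dose handles the labelled syringe.

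**2. Whether the numbers could differ by arm.** CPG 7909 arrives as 1.0 ml vials at 10 mg/ml from the manufacturer (TEST DRUG AND PLACEBO PREPARATION). The placebo is a PBS buffer (CONTROLS). Supplies list them as two separate items of 141 doses each. Separate numbers are therefore plausible. The text does not say so outright, and it does not say the opposite.

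**3. Whether any section neutralises them.** I looked for a statement that the numbers are coded, common to both arms, or linkable only by the pharmacy. The sections on preparation, storage, randomization, immunization, injections, supplies, accountability and code breaking contain none.

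**4. Size of an arm.** The sample size section gives 42 per group and 10% drop-out: 42 / (1 − 0.10) = 46.7, rounded up to 47 per group, and 2 × 47 = 94. Three doses each gives 47 × 3 = 141, which agrees with the supply list.

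**5. How many one code break would expose, if the numbers are arm-specific.**
- Day-specific batches: only those in the same arm prepared on the same day. Doses are ordered by study ID one day ahead and sterility is guaranteed for 24 hours after dispatch, so this would be a few participants.
- One series per arm for the whole trial: the 47 participants in that arm. With only two series in use, the other arm would follow by elimination.

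The Protocol does not say which applies, so the range is from a few to a whole arm. Beyond the single participant concerned, any such exposure defeats the intention in the ENROLMENT section that one allocation can be opened on its own.

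**6. Which outcomes are exposed.**

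| Outcome | Who determines it | Exposed? |
| --- | --- | --- |
| High responder (IgG) | Outside institute, on samples coded by study number | Largely not |
| Solicited symptoms | Participant diary, four days | Largely not |
| Causality of solicited local reactions | Fixed as related | No |
| Intensity of events not in the diary | Investigator | Yes |
| Causality of all other events | Investigator | Yes |
| Clinical significance of laboratory findings | Investigator | Yes |
| Decision to stop further vaccination | Participant or investigator | Yes, in part |

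**The case against.** The best reply is that the Protocol never says the numbers differ by arm. A batch number prepared by the Hospital Pharmacy could be a neutral pharmacy number, the label names no product, and the pharmacy, which holds the list and labels both preparations, could easily number the syringes blindly. The stated blinding rules point towards such an intention. This stands as far as it goes: the risk is conditional. It does not dispose of the point, because the CRF must also hold the exact product number of each test drug or placebo. On its ordinary reading that identifies a product, and staff following the text literally could record arm-specific numbers.

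A reader might infer several stronger things that the Protocol does not support.

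- That the labels already undo the double blind. The text does not establish that the numbers differ, or that the site can link a number to a product.
- That one break necessarily reveals all 47 of an arm. That needs a single series per arm, which is nowhere stated.
- That the 10 to 20 serious adverse events expected make a code break likely. That figure reflects background morbidity. The code may be broken only for a serious event very probably caused by a trial vaccination, or for an unexpected death.
- That blocks of 6 reveal the active group. A 1:1 block splits 3 and 3. It may confirm that there are two groups, but it does not show which is which.
- That the primary comparison is biased. IgG is measured elsewhere on coded samples.

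It is also fair that the Protocol expects only a slight excess of generally mild injection-site reactions at this dose, so tolerability is a weak cue.

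**Conclusion.** The point holds as a conditional weakness in the blinding procedure. The Protocol directs that identifying numbers for test drug and placebo be shown to, and recorded by, people it describes as blinded, and it includes no safeguard that makes those numbers uninformative.

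The consequence rests on one assumption, that the numbers are specific to an arm. This is plausible for two separately sourced preparations, but it is not stated. Under it, one code break exposes between a few participants and a whole arm of 47, depending on how batches are formed. The harm would fall mainly on investigator-judged safety outcomes and on decisions to stop vaccination. The IgG endpoint and the diary-based symptoms are largely protected, so this is not a threat to the primary result. It should be corrected because safety of the adjuvant is an objective in its own right and the correction is nearly free.

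**What to change.** Label each test drug or placebo syringe with study ID, dispatch time and a pharmacy-generated code that carries no information about arm, for example one unique to each syringe. Replace the CRF fields for product and batch number of test drug or placebo with that code. Keep the actual product and batch numbers in the unblinded pharmacy log, linked by study ID, and merge them only after unblinding. Amend IMMUNIZATION and VACCINES AND TEST DRUG/PLACEBO INJECTIONS so that both say this.

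If the pharmacy's numbers are already neutral, a sentence saying that they are not arm-specific and that the key stays in the pharmacy would close the gap in the text. The reference to an exact product number would still need rewording.

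The cost is a change to the label template and a CRF field. The pharmacy already prepares and labels both preparations and holds the randomization list, so traceability and the end-of-study stock reconciliation are kept without added staff.

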**ACCESS TO AND STORAGE OF RANDOMIZATION ENVELOPES**

Randomization envelopes will be locked away at the Department of Infectious Diseases, Skejby hospital – Aarhus University Hospital, [name]. Access to randomization envelopes can be granted through contact to the study investigators or in rare cases (i.e. if primary and co-investigators are unavailable) thru the senior Infectious Disease physician on call.

**DURATION OF TRIAL FOR EACH PARTICIPANT:** 10 months from 1st vaccination to last follow-up.

##### SUBJECT WITHDRAWAL FROM THE STUDY:

From an analysis perspective, a “withdrawal” from the study is any subject who did not come back for the concluding visit foreseen in the protocol.

A subject qualifies for “withdrawal” from the study when no study procedure has occurred, no follow-up has been performed and no further information has been collected for this subject from the date of withdrawal/last contact.

Investigators will make an attempt to contact those subjects who do not return for scheduled visits or follow-up.

Information related to the withdrawal will be documented on the Study Conclusion page on the CRF. The investigator will document whether the decision to withdraw from the study was made by the subject or the investigator and which of the following possible reasons was responsible for the withdrawal:

- Participant’s withdrawal of informed consent
- Protocol violation
- A serious adverse event (SAE)
- Non-serious adverse event
- Lost to follow-up
- Other (specify)

**Withdrawals will not be replaced.**

##### SUBJECT WITHDRAWAL FROM INVESTIGATIONAL PRODUCT

A withdrawal from the investigational product is any subject who does not receive the complete treatment, i.e. when no further planned dose is administered from the date of withdrawal. A subject withdrawal from the investigational product may not necessarily be withdrawn from the study as further study procedures or follow-up may be performed (safety or immunogenicity) if planned in the protocol.

Information related to premature discontinuation of the investigational product will be documented in the CRF. The investigator will document whether the decision to discontinue further vaccination was made by the subject or the investigator and which of the following reasons was responsible for the withdrawal:

- Serious adverse event
- Non-serious adverse event
- Other (specify)

Unblinding of the subject will documented in the CRF.

##### DATA TO BE INCLUDED IN THE CASE REPORT FORM:

- Birthday, sex, race, height, weight, study number
- Adverse events reported by subject including starting point and duration (time to resolution)
- Positive findings during physical examination
- Medical history
- Other vaccinations received outside the study during the study period
- Any changes in regular medication during the time of study
- Pre-existing conditions or signs and/or symptoms present in a subject prior to the start of the study/first vaccination
- All laboratory findings during the time of the study

##### REASONS FOR “BREAKING” A PARTICIPANTS RANDOMIZATION CODE:

- SAE and a strong degree of probability that the event is an adverse reaction to a vaccination received during this trial
- Unexpected death of a study participant

##### SPONSOR’S TERMINATION OF STUDY:

- The sponsor reserves the right to temporarily suspend or prematurely discontinue this study for reasons including, but not limited to, safety or ethical issues or severe recruitment difficulties.

##### PARTICIPANT INCLUSION CRITERIA:

1. Written informed consent and authority statement provided according to local regulatory and ethical practice using a participant information sheet and informed consent form approved by the responsible Ethics Committee.
2. Male or female participants aged >= 18 years.
3. HIV-seropositive individuals

##### PARTICIPANT EXCLUSION CRITERIA:

1. Pregnancy as determined by a positive urine beta-hCG (if female).
2. Participant unwilling to use reliable contraception methods for the duration of the trial. Reliable methods of birth control include: pharmacologic contraceptives including oral, parenteral, and transcutaneous delivery; condoms with spermicide; diaphragm with spermicide; surgical sterilization; vaginal ring; intrauterine device; abstinence; and post-menopause (if female).
3. Currently breast-feeding (if female).
4. Latest CD4 count < 200 x106 cells/µL
5. Viral load (HIV RNA) > 50 copies/mL **if** on HAART (defined as at least three antiretrovirals including either a protease inhibitor or a NNRTI, i.e. combivir 300/150 mg x2 + stocrin 600 mg x1 for a minimum of 6 months)
6. Previous enrollment in this study.
7. Any medical, psychiatric, social, or occupational condition or other responsibility that, in the judgment of the Principal Investigator (PI), would interfere with the evaluation of study objectives (such as severe alcohol abuse, severe drug abuse, dementia).
8. Unable to follow protocol regimen
9. Pneumococcal vaccination 5 years or less prior to inclusion
10. Planned participation in other vaccination trials during the time of the study

##### PROCEDURES:

Consenting participants that pass the inclusion/exclusion criteria will be enrolled in the study. Blood samples for baseline parameter measurements will be drawn before proceeding to immunization.

At randomization, participants will be allocated 1:1 one of two study regimens:

- **Experimental group**: Double paediatric dose of 7-valent conjugate pneumococcal vaccination (Prevenar®, Wyeth) + 1 mg CPG 7909 (day 0), double paediatric dose of 7-valent conjugate pneumococcal vaccination (Prevenar®, Wyeth) + 1 mg CPG 7909 (day 90) and single dose of 23-valent polysaccharide vaccine (Pneumo Novum®, Sanofi Pasteur MSD) + 1 mg CPG 7909 (day 270)
- **Control group**: Double paediatric dose of 7-valent conjugate pneumococcal vaccination (Prevenar®, Wyeth) + 100 μl of placebo (day 0), double pediatric dose of 7-valent conjugate pneumococcal vaccination (Prevenar®, Wyeth) + 100 μl of placebo (day 90) and single dose of 23-valent polysaccharide vaccine (Pneumo Novum®, Sanofi Pasteur MSD) + 100 μl of placebo (day 270).

Blood samples are drawn and follow-up by the physician includes physical examination and medical history, registration of AEs/SAEs, vaccination history outside the study and any other information that may be relevant to document in the CRF. A concluding visit is scheduled at day 300.

A subject who returns for the concluding visit or is available for the concluding contact foreseen in this protocol is considered to have completed the study.

##### VACCINES AND TEST DRUG/PLACEBO INJECTIONS:

All subjects are dosed at 0, 90 and 270 days. All immunizations are done in the deltoid muscle of the right or left arm (according to the participants preference).

- At day 0 and 90 study participants receive one intramuscular injection of double the recommended paediatric dose of Prevenar 1.0 ml + 0.1 ml test drug (CPG 7909)/placebo. In both cases, the volume injected into the arm is 1.1 ml.
- At day 270 study participants receives one intramuscular injection of 0.5 ml Pneumo Novum + 0.1 ml test drug(CPG 7909)/placebo. In all cases, the volume injected into the arm is 1.1 ml.

Investigators and participants are not aware of whether experimental or control injection is administered. The volume and appearance of each injection product are identical. The exact product number of each test drug/placebo and batch number prepared by the hospital pharmacy will be recorded in the individuals CRF as well as the volume of any remaining fluid in the syringe .

Immunization and follow-up is conducted by investigators and study nurses at the Department of Infectious Diseases at Skejby Hospital, Aarhus University Hospital.

**TEST DRUG(CPG 7909)/PLACEBO AND VACCINE SUPPLIES**

The Hospital Pharmacy Aarhus Hospital, Aarhus University Hospital will supply the following study drug and placebo sufficient number of doses to administer to all subjects as described in the present protocol:

- 141 doses of 0.1 ml CPG 7909 formulated in PBS buffer
- 141 doses of 0.1 ml placebo

At least an additional 10% of their respective amounts will be supplied for replacement in case of breakage, bad storage conditions or any other reason that would make the test drug/placebo or vaccine unusable (i.e. given by mistake to another subject).

Vaccines will be delivered directly to the Department of Infectious Diseases and stored according to manufacturer’s prescriptions.

- 374 doses of 0.5 ml Prevenar, Wyeth
- 94 doses of 0.5 ml Pneumo Novum, Sanofi Pasteur

**TEST DRUG/PLACEBO ACCOUNTABILITY**

At all times the figures on supplied, used and remaining test drug/placebo doses should match. At the end of the study, it must be possible to reconcile delivery records with those of used and unused stocks. An explanation must be given of any discrepancies.

**EVALUATIONS:**

Study assessment will be done by investigators and include: Written informed consent, inclusion/exclusion criteria, medical history, demographics, pregnancy test (Women of childbearing potential only), physical and overall assessment of study eligibility.

